### Outcome measures

The initial assessment includes clinical interview and the following shoulder tests: the Constant–Murley Test (CM) (see Additional file 2) and the Simple Shoulder Test (SST) (see Additional file 3).

#### Primary outcome measures

At 4, 8 and 12 weeks, we will use the CM. The CM is an assessment tool universally used and accepted for shoulder function [32]. We will assess changes in the CM scores from baseline. The CM has a 100-point scoring system that is divided into four domains: pain (maximal 15 points), daily life activities (maximal 20 points), painless range of motion (maximal 40 points) and abduction strength evaluation (maximal 25 points) according to the methods described by Constant [33].

In addition we will use the SST Spanish validated version, an instrument that features 12 one-dimensional Yes/No answer questions [34]. The SST is a short questionnaire (2–3 minutes) — easy to understand and complete — and has validity and comparability with other subjective questionnaires [35]. The total score of 12 questions (2 related to pain, 7 on the force and 3 on the range of motion) [35], where 0 is the worst result and 100 is the best shoulder function measured, is calculated based on the number of positive responses multiplied by 100 [35]. The internal consistency of the test was measured by Cronbach’s alpha = 0.85 [36].

The impact of shoulder disorders can be evaluated from different perspectives. Traditionally, evaluation has been made at the local level, focusing on the functional aspects of the pathology and evaluating the range of motion, strength or pain [37]. Currently, there is an increasing trend towards the use of outcome measures that are subjectively reported by patients, assessing the perception of their own functional status [38]. These questionnaires are becoming widely used tools in the evaluation of treatment both in clinical practice and in medical research [34]. It is critical to employ valid and reliable research measures, and they must also be culturally and linguistically appropriate [39]. Current evidence supports the use of the SST questionnaire for longitudinal studies and clinical trials [34]. The SST is among the three subjective questionnaires that score higher reliability, responsiveness to change and interpretation [34]. In addition, the SST has been translated and cross-culturally adapted into Spanish with adequate psychometric properties [40].

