### Statistical analysis

The trial results will be presented as a summary of the outcomes in each group, along with the estimated effect size and its precision. The statistical analysis will be performed in accordance with both an intent-to-treat analysis and a per-protocol analysis to have the maximum information about the treatment outcomes.

Frequency tables and histograms will present affiliation data for the participants. We will carry out a descriptive statistical analysis of the different variables, using frequency tables, bar charts and sector charts with the aim of having as much information as possible for exploration and analysis.

The study’s central hypothesis will be tested by comparing change in the CM score between the two groups for the intervention shoulder Appendix 1. To compare independent variables between the two groups, the Student’s *t* test will be used if validity criteria are met; otherwise, we will use the non-parametric approach Appendix 2. As other studies have shown [45], significant departures of normality are not expected. The difference in the evolution of the CM score between treatment groups from baseline to 4, 8 and 12 weeks follow-up will be tested using repeated measurements analysis of variance.

A non-inferiority study seeks to determine whether a new intervention is therapeutically equivalent, or not less equivalent, to an existing intervention reference [46]. In this study, the new intervention TR will be compared with the conventional standard of rehabilitation after SIS in Spain.

Studies have presented results on the minimal clinically important differences for shoulder outcome measures (Fig. 2) [47, 48]. Recently, a study showed minimal detectable change ≥10 points in the CM score and a standard deviation (SD, 11.2) for patients with SIS [45]. Therefore, the non-inferiority criteria will be evaluated comparing the differences between groups with a non-inferiority margin of 10 points in the CM score, which is considered to be a clinically relevant change [49, 50].

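### The scoring rule given for the Simple Shoulder Test runs from 0 to 1200, not the 0 to 100 stated in the same sentence; a division by 12 is missing

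*Protocol article*

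**What the plan says.** The SST is described in the protocol article, Methods, under the heading "Primary outcome measures". It follows the CM and is introduced with "In addition we will use the SST Spanish validated version".

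Three statements there bear on the score:

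- The instrument is "an instrument that features 12 one-dimensional Yes/No answer questions".
- The item count is repeated with a breakdown: "The total score of 12 questions (2 related to pain, 7 on the force and 3 on the range of motion").
- The scale and the rule then appear in one sentence: a total "where 0 is the worst result and 100 is the best shoulder function measured", which "is calculated based on the number of positive responses multiplied by 100".

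That sentence mentions no division, whether by 12 or by any other number.

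The Statistical analysis section ties the main test to the other instrument: "The study’s central hypothesis will be tested by comparing change in the CM score between the two groups". Non-inferiority is judged "with a non-inferiority margin of 10 points in the CM score".

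**The concern.** A scoring rule should produce the scale it is said to produce, and this one does not. The count of positive answers runs from 0 to 12, so multiplying it by 100 overshoots the stated maximum as soon as a patient gives two positive answers.

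The sentence matters because it is the article's only instruction for turning the answers into a score, and the instrument is listed under the primary outcome heading. The article promises effect sizes with their precision. If the rule went into the study database as printed, the SST results would be reported in units that do not match the scale given to the reader. The CM, described just before it, is also a 100-point instrument, so readers are likely to look at the two sets of results side by side.

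**Working it through.** **Inputs** (all from the primary outcome section of the protocol article)

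- Items: 12, each Yes/No. The breakdown agrees: 2 + 7 + 3 = 12. The number of positive answers, k, therefore runs from 0 to 12.
- Stated scale: 0 to 100.
- Stated rule: score = k × 100.

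**Step 1. Try to reproduce the stated scale from the stated rule.**

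- k = 0: 0 × 100 = 0
- k = 1: 1 × 100 = 100, already the stated best score
- k = 2: 2 × 100 = 200, off the scale
- k = 12: 12 × 100 = 1200, which is 1200 / 100 = 12 times the stated maximum

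The lower end agrees with the stated scale and the upper end does not. The 0 to 100 range is not reproduced.

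**Step 2. Express the count as a share of the 12 items.**

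Score = (k / 12) × 100 gives 0, 8.3, 16.7, 25.0, 33.3, 41.7, 50.0, 58.3, 66.7, 75.0, 83.3, 91.7 and 100. This matches the stated scale at both ends. Each item is worth 100 / 12 = 8.3 points.

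**Step 3. Size of the discrepancy if the printed rule were programmed.**

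The ratio of the two rules is (k × 100) / (k × 100 / 12) = 12 for every k above 0. It is a constant, the same in both arms and at every visit. Means, mean differences, standard deviations and confidence limits are all multiplied by 12. For example, a difference of two items between the arms would be reported as 2 × 100 = 200 points instead of 2 × 8.33 = 16.7.

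**Step 4. What a constant factor of 12 does to the planned tests.**

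- Student's t: the difference d and its standard error are both multiplied by 12, so t = 12d / (12 × SE) = d / SE. It is unchanged.
- Standardized effect: 12d / (12 × SD) = d / SD. It is unchanged.
- Rank-based test: multiplying by a positive constant keeps the order of the scores, so it is unchanged.
- Repeated-measures analysis of variance: numerator and denominator mean squares are both multiplied by 12² = 144, so F is unchanged.

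**Step 5. What else in the article depends on the SST score.**

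The central hypothesis concerns change in the CM. The 10-point margin is on the CM. The sample size of 22 per group is built from a CM standard deviation of 11.2, that margin, 90% power and a 5% level. None of these is an SST quantity. The article states no SST margin, threshold or power figure, so no other number in it becomes wrong.

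**The case against.** The strongest reply is that the slip corrects itself. The scale and the item count stand beside the rule, and the division by 12 reconciles them. Anyone entering data would see at the first patient that scores exceed 100. The wording reads as a condensed description of a cited method rather than a database specification. The article also refers to Additional file 3 for the SST; that file is not shown and may carry the correct rule.

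Most of this stands, and it limits the weight of the point. It does not remove it. The article did not leave the scoring to the supplement: it printed a rule, and the rule conflicts with the scale in its own sentence. If the supplement is right, the article disagrees with it and still needs correcting.

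Three stronger readings are tempting, and the documents do not support them:

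- **That the trial's SST results are inflated 12-fold.** This would follow only if the printed rule were programmed literally, and nothing in the article shows that it was.
- **That a primary conclusion is at risk because the SST is listed as primary.** The heading does cover the SST, but the central hypothesis and the margin are set on the CM alone. A constant rescaling would not change an SST p-value either.
- **That the rule also mishandles unanswered items, so the denominator should be the number of items answered.** The article says nothing about skipped items, which is a matter commonly left to the analysis plan. Its own figures support division by the 12 items and no other denominator.

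**Conclusion.** The point holds as a minor error of stated arithmetic. As printed, the rule gives 0 to 1200 and contradicts the 0 to 100 scale in the same sentence, by a factor of 12 at the top.

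The practical consequence is conditional. It arises only if the printed rule is applied literally, and it is then confined to raw-scale SST values. The exact factor of 12 is measured against (k / 12) × 100. That formula is inferred from the article's own item count and scale; the cited scoring source and Additional file 3 were not available to confirm it.

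**What to change.** Replace the scoring clause with: SST score = (number of positive responses / 12) × 100, range 0 to 100, 8.3 points per item. Confirm that the study database uses this formula and that Additional file 3 agrees with it.

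The cost is one corrected clause and one check of the database formula. No design feature, sample size or test has to change. If scores had already been stored under the printed rule, dividing them by 12 would put them on the stated scale.

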#### Other pre-specified outcome measures

The acceptance and usability of telemedicine applications are prerequisites for identifying potential clinical benefits of this technology. Consequently, it is important to supplement this research with tools to examine the satisfaction and perception of patients [41]. We will use a Spanish adaptation of the Telemedicine Satisfaction and Usefulness Questionnaire (TSUQ) psychometric analysis, which supports the construct validity and internal consistency reliability and is available in English and Spanish [41] (see Additional file 4). This instrument has shown high reliability (Cronbach 0.8) and validity evidence regarding perceptions on telemedicine [42].

To evaluate the cost-effectiveness of telerehabilitation intervention, we will follow international guidelines for conducting cost analyses in randomized clinical trials [43]. This economic analysis is based on the perspective of the health sector, which means that only health intervention costs will be considered. Therefore, only the costs associated with the provision of health services in the traditional physiotherapy and the telerehabilitation group will be taken into account [44]. We will try to have similar baseline characteristics between the groups.

### Data collection and sources of data

Once patients are informed and randomly assigned to one group, we will be able to collect data for statistical analysis. This data collection will take place in the period from October 2016 to March 2017. An independent evaluator in the rehabilitation services will conduct initial assessment and the different measures at 4, 8 and 12 weeks. The data will be added to the database created for that purpose and administered by the principal investigator for statistical analysis.

### Statistical analysis

The trial results will be presented as a summary of the outcomes in each group, along with the estimated effect size and its precision. The statistical analysis will be performed in accordance with both an intent-to-treat analysis and a per-protocol analysis to have the maximum information about the treatment outcomes.

Frequency tables and histograms will present affiliation data for the participants. We will carry out a descriptive statistical analysis of the different variables, using frequency tables, bar charts and sector charts with the aim of having as much information as possible for exploration and analysis.

The study’s central hypothesis will be tested by comparing change in the CM score between the two groups for the intervention shoulder Appendix 1. To compare independent variables between the two groups, the Student’s *t* test will be used if validity criteria are met; otherwise, we will use the non-parametric approach Appendix 2. As other studies have shown [45], significant departures of normality are not expected. The difference in the evolution of the CM score between treatment groups from baseline to 4, 8 and 12 weeks follow-up will be tested using repeated measurements analysis of variance.

A non-inferiority study seeks to determine whether a new intervention is therapeutically equivalent, or not less equivalent, to an existing intervention reference [46]. In this study, the new intervention TR will be compared with the conventional standard of rehabilitation after SIS in Spain.

Studies have presented results on the minimal clinically important differences for shoulder outcome measures (Fig. 2) [47, 48]. Recently, a study showed minimal detectable change ≥10 points in the CM score and a standard deviation (SD, 11.2) for patients with SIS [45]. Therefore, the non-inferiority criteria will be evaluated comparing the differences between groups with a non-inferiority margin of 10 points in the CM score, which is considered to be a clinically relevant change [49, 50].

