**Fig. 2 Fig2:**
[figure not shown]
Example of customized telerehabilitation programme

Based on these data, we performed a calculation of the sample size. According to [45], an SD of 11.2 in the improvement of the CM would be expected. Anticipating a non-inferiority difference of 10 points on that test, a 90% power and the usual significance level of 5%, a sample size of 22 patients per group is needed. Anticipating a dropout rate of 15% (which will be studied by intention to treat), a total of 44 patients will be included (*n* = 44).

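### The comparison of CM change does not adjust for baseline CM; it is valid and meets its stated power, but adjustment would usually narrow the interval set against the 10-point margin

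*Protocol article*

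**What the plan says.** - **Outcome.** Under Primary outcome measures: "We will assess changes in the CM scores from baseline", with assessments at 4, 8 and 12 weeks.
- **Baseline.** CM is part of the initial assessment. Under Outcome measures, "The initial assessment includes clinical interview and the following shoulder tests" introduces a list that names CM and SST.
- **Main comparison.** Under Statistical analysis: "central hypothesis will be tested by comparing change in the CM score between the two groups". The next sentence, on two-group comparisons in general, says that Student's t "test will be used if validity criteria are met; otherwise, we will use the non-parametric approach". No covariate is named.
- **Course over time.** The difference in evolution from baseline to 4, 8 and 12 weeks of "follow-up will be tested using repeated measurements analysis of variance". Baseline is one of the time points here, not a covariate.
- **Criterion.** A "non-inferiority margin of 10 points in the CM score".
- **Sizing.** In the sample-size paragraph after Fig. 2, "an SD of 11.2 in the improvement of the CM would be expected". With 90% power and a 5% level this gives 22 per group. The total is 44, with 15% dropout anticipated.

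**The concern.** A change score subtracts the whole baseline value, which amounts to fixing the regression slope of follow-up on baseline at 1. If the true slope differs from 1, part of any chance difference in baseline CM stays in the treatment estimate, and the residual variance is larger than it need be. The slope is r × SD(follow-up) / SD(baseline), so a correlation below 1 does not by itself put the slope below 1; the SD ratio matters too.

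The randomisation section describes a computer-generated sequence and sealed envelopes, with no stratification on baseline CM. With 22 patients per arm, appreciable chance differences in baseline CM are to be expected. The non-inferiority verdict depends on where one confidence limit falls relative to 10 points, so avoidable width matters.

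**Working it through.** **Inputs.** From the article: margin 10, SD of change 11.2, 22 per group, 44 in total, 15% dropout. Not in the article, so assumed: r (0.3 to 0.9) and k = SD(baseline) / SD(follow-up). True difference 0 throughout.

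**1. The plan's own figure.** n per group = 2 × [11.2 × (1.645 + 1.282) / 10]² = 21.5, rounded up to 22, at one-sided 5%. At one-sided 2.5% the same formula gives 26.4, so 27. The stated 22 therefore corresponds to one-sided 5%. Power of the change-score t test with 22 per group is 89.8% (noncentral t), or 90.6% by the normal approximation. The SD used is that of the improvement, which is the right SD for a change-score test.

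**2. Variance ratio, adjusted against change score.** Let s be the follow-up SD.

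- Var(change) = s²(1 + k² - 2rk)
- Residual variance given baseline = s²(1 - r²)
- Ratio = (1 - r²) / (1 + k² - 2rk), which becomes (1 + r)/2 when k = 1

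| k | r = 0.3 | r = 0.5 | r = 0.7 | r = 0.9 |
|---|---|---|---|---|
| 0.5 | 0.958 | 1.000 | 0.927 | 0.543 |
| 0.75 | 0.818 | 0.923 | 0.995 | 0.894 |
| 1 | 0.65 | 0.75 | 0.85 | 0.95 |
| 1.25 | 0.502 | 0.571 | 0.628 | 0.608 |

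The ratio is 1 exactly where the slope r/k is 1. For example, k = 0.5 and r = 0.5 gives 0.75 / 0.75 = 1.00.

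**3. Power with equal SDs.** The adjusted SD is 11.2 × √((1 + r)/2) = 9.03, 9.70, 10.33 and 10.92 at the four values of r. Power is by noncentral t. The adjusted model loses one degree of freedom (N - 3) and carries the expected variance factor 1 + 1/(N - 4). With 15% lost, 44 × 0.85 = 37.4, so about 37 evaluable patients, or 18.5 per arm.

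| | Change score | r = 0.3 | r = 0.5 | r = 0.7 | r = 0.9 |
|---|---|---|---|---|---|
| 22 per arm, one-sided 5% | 89.8% | 97.3% | 95.3% | 93.0% | 90.4% |
| 18.5 per arm, one-sided 5% | 84.6% | 94.6% | 91.7% | 88.5% | 85.2% |
| 18.5 per arm, one-sided 2.5% | 75.2% | 89.7% | 85.1% | 80.5% | 76.0% |

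If r were 1 with equal SDs, adjustment would cost a little: 89.1% against 89.8% with 22 per arm.

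**4. Effect of a chance baseline difference, equal SDs, 22 per arm.** From Var(change) = 2s²(1 - r) = 11.2², s = 9.47, 11.20 and 14.46 at r = 0.3, 0.5 and 0.7. One standard error of the baseline difference is s × √(2/22) = 2.85, 3.38 and 4.36 points. The change-score estimate moves by (1 - r) times that: 2.0, 1.7 and 1.3 points. For scale, the one-sided 5% limit lies 1.682 × 11.2 × √(2/22) = 5.7 points from the estimate.

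**The case against.** The strongest reply is that nothing here is wrong. Several stronger readings are tempting, and the article does not support them.

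- **That the t test loses power against plan.** It does not. The 22 per group was computed with the SD of the improvement and gives 89.8% for that test. The fall to about 85% arises because 44 = 2 × 22 contains no allowance for the 15% dropout. The fall to about 75% adds a stricter level. Neither comes from the choice of test.
- **That chance imbalance biases the result.** Under randomisation the change-score difference is unbiased, and its standard error already contains the imbalance. The shifts in step 4 of the working describe sampling error that adjustment can remove, not a systematic error.
- **That the gain is known, or free.** It depends on r and k, and the article gives neither. At k = 0.5, r = 0.5 there is no gain, and at k = 0.75, r = 0.7 almost none. Adjustment costs one degree of freedom and must be pre-specified.
- **That the plan relies on an intention to balance the arms.** "We will try to have similar baseline characteristics between the groups" closes the cost-effectiveness paragraph and is not offered as control of CM imbalance.

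It can also be said that the t test stands in a general sentence not expressly tied to the central hypothesis, that comparing change does not exclude a covariate, and that an analysis plan not shown may name one. This lowers the weight of the point. It does not remove it: the article states how the main comparison is made and names tests that take no covariate. The repeated-measures analysis does not fill the gap, because with baseline as a time point its group-by-time contrasts again compare changes.

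**Conclusion.** The point holds as a recommended improvement in efficiency, not as an error. The planned comparison is valid and meets its stated power at one-sided 5%. Adjusting for baseline CM is generally at least as precise, apart from the small degree-of-freedom cost, and it removes the effect of chance baseline imbalance. With equal SDs the variance falls by 35%, 25%, 15% or 5% at r = 0.3, 0.5, 0.7 or 0.9; with unequal SDs the reduction may be larger or nil.

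Adjustment may partly or fully offset the uninflated dropout. At one-sided 5% with 18.5 per arm and equal SDs, power is 90.1% at r = 0.6 and 88.5% at r = 0.7, so 90% is regained only if r is about 0.6 or lower. At one-sided 2.5% it is just short of 90% even at r = 0.3. Since r and k are unknown, adjustment is no substitute for correcting the sample size. All power figures assume a true difference of zero and an SD of change of 11.2.

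**What to change.** Pre-specify as the primary estimate the treatment coefficient from a linear model of 12-week CM on treatment and baseline CM, and compare its confidence limit with -10 (telerehabilitation minus physiotherapy). Modelling the 12-week change on the same terms gives the same coefficient, so the wording about change can stay. Use the same model for SST.

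The cost is one degree of freedom and a change of wording made before the analysis. Baseline CM and SST are already collected, and the article reports enrolment as ongoing. The timing of the baseline assessment relative to randomisation and the dropout allowance in the sample size are separate matters that this change does not settle.

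### The plan lets undefined checks on the observed data choose a t test or an unnamed non-parametric method, apparently for the primary Constant–Murley comparison; if that fallback is a rank test, it does not test the mean difference on which the margin and sample size rest.

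*Protocol article*

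**What the plan says.** All of this is in Methods, Statistical analysis, of the protocol article.

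- The central "hypothesis will be tested by comparing change in the CM score between the two groups for the intervention shoulder".
- The next sentence opens "To compare independent variables between the two groups" and says that the t test "will be used if validity criteria are met; otherwise, we will use the non-parametric approach", with a pointer to Appendix 2. The text does not define the validity criteria or name the non-parametric method. The section adds that marked non-normality is not anticipated, citing an earlier study.
- Change over 4, 8 and 12 weeks is also to be analysed by repeated-measures analysis of variance.
- Non-inferiority is judged by "comparing the differences between groups with a non-inferiority margin of 10 points in the CM score". The summary measure (mean or other) is not named.
- The sample-size paragraph states that "an SD of 11.2 in the improvement of the CM would be expected", takes "a 90% power and the usual significance level of 5" per cent, and concludes that "a sample size of 22 patients per group is needed".

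The section promises an effect size with its precision. It does not say which of these analyses decides non-inferiority.

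**The concern.** In a non-inferiority trial the margin has meaning only for the quantity it was set on. Here the data would select the test, and the two branches can address different quantities. The t test concerns the difference in mean change. A rank test concerns how often a patient in one arm scores above a patient in the other or, in its shift form, the median of all pairwise differences. These agree when the arms differ only by a shift and part company when they differ in shape.

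One shape difference deserves thought in this trial. The telerehabilitation (TR) arm has three videoconference sessions and then exercises alone, while the physiotherapy (PT) arm is treated one to one, and the Discussion anticipates technical difficulties. If a minority of TR patients recovered poorly while the rest did well, the mean would register it. The same tail would also make a normality check more likely to fail and so bring in a rank measure that discounts it. TR could then be called non-inferior with a mean deficit at the margin. The tested quantity would also not be fixed until the data were in.

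**Working it through.** **1. What quantity the margin and sample size imply.** Inputs from the sample-size paragraph: margin 10, SD 11.2, power 90%, significance level 5% (one- or two-sided not stated). Assumed true difference: 0.

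n per group = 2(z₁₋α + z₁₋β)² × SD² / margin²

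- One-sided 5%: 2 × (1.645 + 1.282)² × 11.2² / 10² = 21.5, so 22. This matches the plan; power at 22 is 90.6%.
- One-sided 2.5%: 2 × (1.960 + 1.282)² × 11.2² / 10² = 26.4, so 27. This does not match.

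The stated 22 is therefore a mean-difference calculation at one-sided 5%, although the text never uses the word mean.

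**2. What a rank fallback would test.** An ordinary Mann–Whitney test has no difference as its null hypothesis. Neither outcome speaks to a 10-point margin, and this needs no simulation. Adding 10 points to each TR value and then testing brings the margin in, but the target is now the median pairwise difference θ. Suppose PT is normal with SD 11.2 and a share p of TR patients sit d points lower, the rest equal to PT. The mean deficit is p × d, and θ solves

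(1 − p) Φ(−θ/(11.2√2)) + p Φ((−d − θ)/(11.2√2)) = 0.5

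For p = 0.20, d = 50, the mean deficit is 10. At θ = −5.0 the left side is 0.8 × 0.624 + 0.2 × 0.002 = 0.50. So the rank shift is −5.0 while the mean difference is −10. For p = 0.25, d = 40 it is −6.6; for p = 1/3, d = 30 it is −8.6.

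**3. False non-inferiority.** Assumptions not in the documents: Shapiro–Wilk at 5% in each arm as the validity check; Mann–Whitney on data shifted by 10 as the fallback; 22 analysed per arm; true mean deficit exactly 10; one-sided 5%; 20,000 simulated trials per row. Overall TR SD = √(11.2² + p(1 − p)d²).

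| Poor tail in TR only | TR SD | Rank test triggered | t test alone | Shifted rank test alone | Data-chosen test |
|---|---|---|---|---|---|
| None (normal, SD 11.2) | 11.2 | 10% | 4.9% | 4.7% | 5.1% |
| 1/3 of patients, 30 points | 18.0 | 19% | 5.7% | 9.4% | 7.6% |
| 25%, 40 points | 20.6 | 48% | 6.2% | 17.0% | 14.5% |
| 20%, 50 points | 22.9 | 81% | 7.3% | 27.5% | 26.3% |

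At one-sided 2.5% the last column becomes 2.4%, 4.3%, 9.1% and 17.4%.

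**4. Moving the tail.** Same set-up, 6,000 trials per case, rates for the data-chosen test. Where two figures are given, they are for 25%/40 points and 20%/50 points.

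- Same poor tail in both arms: 4.8% and 4.7%, although the rank test is triggered in 70% and 96% of trials.
- Poor tail in PT only: 3.1% and 1.6%.
- Upper tail in TR: 3.2% and 1.4%.
- Skewed (gamma) data in both arms, SD 11.2: 5.3%.
- A 10% poor tail in PT and a larger one in TR: 9.3% (40 points) and 16.1% (50 points).

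**5. Smaller spread.** If the SD within each component, and in PT, is 6–8 rather than 11.2, the overall TR SD is about 11.6–13 and the rate with a poor TR tail is about 9% to 26%. Inflation is thus possible without a doubled TR SD, but then PT must be less variable than the plan assumes.

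**The case against.** A reader might infer that this plan carries a 15–26% false non-inferiority rate and that the error always favours TR. The documents support neither.

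- **Direction.** Inflation needs a poor tail wholly or mainly in TR. Tails shared by both arms leave the rate near 5%, and a poor tail in PT or an upper tail in TR makes the rule conservative.
- **Size.** The upper figures need a fifth to a quarter of TR patients to be 40–50 points worse on a 100-point scale, the rest equal to PT, and a TR SD about twice the documented 11.2. No section says this is likely, and the article expects no marked non-normality. Under its own normal model nothing is lost. Part of the excess would also remain without the data-driven choice, since the t test alone gives about 6–7% in those cases.
- **Procedure.** The article names neither Shapiro–Wilk nor Mann–Whitney nor a shift by the margin. Appendix 2 is not shown. A bootstrap or permutation interval is also non-parametric and could keep the mean difference.
- **Scope.** The sentence speaks of independent variables. Its place between the central hypothesis and the remark on normality makes the CM comparison the likely target, but this is not explicit. Nor does the article say that the selected test decides non-inferiority.

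All of this stands as a limit on size and certainty. It does not remove the defect: the article states a rule under which the data choose the method, and does not tie both branches to one quantity. The expectation of near-normality does not rescue the rule either. If it is right, the rule is not needed; if it is wrong, the rule can do harm.

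**Conclusion.** The concern holds in limited form. As written, undefined criteria applied to the observed data select the test, apparently for the primary CM comparison, while the margin and the 22 per group imply a difference in mean change. If the fallback is a rank test, it either ignores the 10-point margin or applies it to another quantity.

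The consequence should be stated as a scenario range: about 5% with normal data or a common tail, about 8% with one third of TR patients 30 points worse, about 15–26% with 20–25% of them 40–50 points worse, and below 5% if the poor tail is in PT. These figures rest on the assumed Shapiro–Wilk trigger, the shifted Mann–Whitney test, one-sided 5% and a true mean deficit of exactly 10. They are not predictions for this trial. The point is worth correcting before analysis because the quantity under test should be fixed in advance and the change is small.

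**What to change.** Delete the data-driven choice of test for the primary comparison and state: non-inferiority is decided on the confidence interval for the difference in mean CM change (t-based, Welch or baseline-adjusted, one of them chosen in advance) against the 10-point margin, whatever the shape of the distribution; a bootstrap interval for the same mean difference is the sensitivity analysis; rank-based results are descriptive and are not read against the margin.

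The cost is one or two sentences, with no new data or patients. With normal data at 22 per arm the t test has about 90% power in simulation, as planned. The small downside is reliance on a t-based interval under skewness with 22 per arm: in the scenarios above its error was 5.7–7.3% against a nominal 5%. The bootstrap interval serves as a check on this.
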